**D. Physical Activity Questionnaire:**

- *Minnesota Leisure Time Physical Activity:* This is a checklist of 60 physical or recreational activities subjects may have participated in over the last 12 months.

**Study Testing Visits 3-6: (each visit will last about 6 hours):**

**The following information will be provided to the subject**

- While the subject is in the study, they will be asked to maintain their normal physical activity level.
- Subjects will be asked to follow a special diet for 1 day before study testing visits 3, 5 and 7. The diet will require subjects to eat at least 200 grams of carbohydrate each day while limiting the amount of fat ingested. Subjects will be given a chart to help record their carbohydrate and food intake and must return the chart on the day of their admission.
- **Subjects must not drink alcoholic or caffeinated beverages for 24 hours before the study testing visit begins** (i.e. after 7am the day before the test).
- **Subjects** **must not use allergy or pain-related medicines (over-the-counter or prescription**) for at least 5 days prior to each admission.
- **Subjects must not use antibiotics for 3-4 weeks before study testing visits.** If subjects have been prescribed an antibiotic 3-4 weeks before the study or are prescribed an antibiotic during the study they should inform the investigators. This may result in an inability to collect fecal matter for gut microbiota analysis.
- **Subjects must not use statins, glucose lowering medication, or antioxidant dietary supplements 24 hours before the study testing.**
- **Subjects must not perform any vigorous exercise for 48 hours prior to each test day**.
- The tests must be performed in the fasted state, so subjects may not eat or drink anything (except water) after about 7pm the night before.
- Subjects will be asked to report to the CRU by approximately 7:00am on the morning of each test.
- If a subject is a pre-menopausal woman, they will be asked to report to the CRU to provide a urine sample for a pregnancy test. The test must be negative in order for them to continue their participation.

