
# Hypothesis to be Tested

The central hypothesis is that pre-operative metabolic health is an important predictor of bariatric surgery effectiveness. We hypothesize that there is an adipose-derived immunosignature that predicts post-operative recurrence of obesity related CVD abnormalities and that targeting reductions in obesity BEFORE surgery will enhance the success of bariatric surgery on this disease risk. We expect that the combination of exercise and diet will be more successful at improving insulin sensitivity and reducing immune cell dysfunction compared to diet alone as well as expect that exercise will be superior to standard of care alone. These separate studies are expected to provide unique insight to the mechanism by which diet and/or exercise impact immune metabolism in obese patients, and this will shape the development of future studies in bariatric patients per se.

Primary Objectives:

1. **Ascertain the effects of Ex+CR vs. CR in obese subjects and Ex vs. standard of care (SC, i.e. control) BEFORE surgery on cardiometabolic risk.**
2. **Examine the effects of Ex+CR vs. CR in obese subjects and Ex vs. standard of care (SC, i.e. control) BEFORE surgery on surgical complications and quality of life.**
3. **Determine if circulating immunophenotyping after Ex+CR vs. Ex vs. CR vs. SC correlate with immune composition of adipose cell depots (omental and subcutaneous) at the time of surgery or post-intervention testing**.

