**4. What is your plan for primary variable analysis?**

***Analysis between weight loss, insulin sensitivity and immune health:***

Data will be analyzed using R (Vienna, Austria, 2011). A two-way repeated measures analysis of variance (ANOVA) will be used to assess time course differences (group x test) for **AIM 1** and **AIM 2**. A repeated measures ANOVA will also be used to assess differences in adipose cell depot among groups (**AIM 3**). Bonferonni post-hoc analysis will be used to determine group differences and paired t-tests will be used to assess within treatment effects. Linear regression analyses will be used to identify relationships between respective variables. A *P*<0.05 will be considered statistically significant. Data will be expressed as mean ± SEM.

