***Phase 2: SCREENING AND STUDY TESTING PROCEEDURES***

**Study Test Visit 2 (this visit will last about 2 hours)*:***

**Subjects must fast (not eat) for 4 hours before this visit.**

The second screening visit will start with a:

- Review of the subject’s medical history
- Physical exam and vital signs (blood pressure, heart rate and resting electrocardiogram)
- If subjects are women who are able to bear a child, they will have a urine pregnancy test that must be negative in order to participate.

The purpose of the physical exam is to determine if subjects are eligible for the exercise portion of the study and that it is safe for them to participate. The pregnancy test must be negative in order for the subjects to participate. If subjects continue to qualify for the study the remainder of the visit will involve the study procedures described below:

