***Phase 5: Post-Intervention Testing***

All study testing visits highlighted above in phase 2 will be repeated.

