***Phase 7: Post-Bariatric Surgery Testing (if applicable)***

After bariatric surgery, the subjects will repeat phases 3 and 5 as part of post-operation testing to determine if pre-operative therapy impacts post-surgery metabolic outcomes.

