***Total payment***: **$450 (or $500 if fat biopsy performed in phase 3)**

Non-Bariatric subjects will be compensated per completion of phases:

Completion of Phase 1-3: $**50 (or $75 if pre-test fat biopsy performed)**

Completion of Phase 4-5: $**50 (or $75 if post-test biopsy performed)**

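### The one-day carbohydrate lead-in is tied to visits 3, 5 and 7, but only visit 3 is a tolerance test in any arm; phases 3, 5 and 7 were probably meant

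*Protocol*

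**What the plan says.** Under Study Testing Visits 3-6, in the information to be given to subjects, the protocol states: "Subjects will be asked to follow a special diet for 1 day before study testing visits 3, 5 and 7". The diet sets a minimum of 200 g carbohydrate and keeps fat low; subjects chart their intake and return the chart when admitted.

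The two Study Schedule Visit Overview tables fix when the tolerance tests occur. Bariatric subjects have the MMTT at pre-test visit 3, at post-intervention visit 4 (12 in the exercise arm) and at post-surgery visit 6 (14 in the exercise arm). Non-bariatric subjects have the OGTT at visit 3 and at visit 6 (18 with exercise). The Blood draws text gives the same two visits for the non-bariatric microparticle samples.

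The protocol also numbers phases. Phase 5 is post-intervention testing, described as "All study testing visits highlighted above in phase 2 will be repeated". Phase 7 is post-surgery testing, in which "the subjects will repeat phases 3 and 5 as part of post-operation testing". Phase 3 has no heading of its own in the text shown.

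**The concern.** The visit list does not fit the schedules. It names visits that are not tests, omits every test after baseline, and includes a visit 7 that lies outside the section's own heading.

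The tests affected supply glucose AUC, insulin AUC and the insulin sensitivity index, the first three outcomes listed for the primary objective under Statistical Considerations. Under the plan for primary variable analysis, "paired t-tests will be used to assess within treatment effects". If only the baseline test has a carbohydrate lead-in, a pre/post change in these measures reflects both the intervention and the changed preparation. The main effect of test in the repeated measures ANOVA is exposed in the same way.

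The risk is easiest to see in the two diet arms, whose prescribed intake during the intervention is 1000-1400 kcal a day. A subject on that plan is unlikely to take a carbohydrate-rich day before the final test unless told clearly to do so.

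**Working it through.** No sample size or power figure is involved. The check sets the diet rule beside the schedules and then beside the phase numbers.

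**Read as visit numbers**

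| Arm | Tolerance-test visits | Overlap with {3, 5, 7} | Visit 5 is | Visit 7 is |
|---|---|---|---|---|
| Standard care (bariatric) | 3, 4, 6 | 3 | surgery | non-existent |
| Exercise (bariatric) | 3, 12, 14 | 3 | training (visits 4-11) | training |
| Diet (non-bariatric) | 3, 6 | 3 | diet pick-up (visits 4-5) | non-existent |
| Diet + exercise (non-bariatric) | 3, 18 | 3 | training (visits 4-17) | training |

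- Tests covered: 1 of 3 per bariatric subject and 1 of 2 per non-bariatric subject, in each case the baseline test.
- Visits 5 and 7 across four arms give 2 × 4 = 8 slots: 4 training + 1 surgery + 1 pick-up + 2 non-existent = 8. Tolerance tests among them: 0.

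The schedule notes allow visit 2 to be split over two days. This does not rescue the list, since in both exercise arms visits 5 and 7 sit inside the printed training blocks.

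**Read as phases**

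- Phase 3 is the pre-test. The Payment section places the pre-test fat biopsy there ("or $500 if fat biopsy performed in phase 3"), and the bariatric schedule puts that biopsy at pre-test visit 3. The Phase 7 text also treats phase 3 as something repeated after surgery.
- Phase 5 is post-intervention testing: visit 4 (standard care), 12 (exercise), 6 (diet) or 18 (diet + exercise).
- Phase 7 is post-surgery testing, bariatric only: visit 6 (standard care) or 14 (exercise).
- Tests covered: 3 of 3 bariatric and 2 of 2 non-bariatric.

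**Tension with the diet arms**

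Taking 4 kcal per gram of carbohydrate as an assumption, 200 g × 4 = 800 kcal. That is 800/1400 = 57% to 800/1000 = 80% of the daily allowance.

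**Companion point**

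Blood draws specifies sampling every 30 minutes to 180 minutes, which includes a 150-minute sample. Glucose Metabolism tests lists five post-drink draws at 30, 60, 90, 120 and 180 minutes, which does not. These are two grids for the same AUC; no bias is shown from this.

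**The case against.** The strongest reply is that this is a labelling slip and nobody would carry it out as printed. Visit 7 does not exist in two arms, and visit 5 is surgery in one. The rule speaks of testing visits and of a chart returned at admission, which does not describe a gym session. Neighbouring preparation rules attach to every test or admission. The section also sits under "Phase 2: SCREENING AND STUDY TESTING PROCEEDURES", whose testing visits are repeated in Phase 5, so the preparation arguably carries over. Much of this stands, and it makes the harm conditional. It does not make the list right: the diet is the one preparation rule restricted to numbered visits, and it is among the information meant for subjects.

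Second, the main comparisons are between arms. The first primary objective is to "Ascertain the effects of Ex+CR vs. CR in obese subjects and Ex vs. standard of care", and the mismatch is identical within each pair. This also stands: the group-by-test interaction is largely protected, provided the preparation effect is similar in both arms. Diet records at every tolerance-test visit would reveal unequal intake afterwards.

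Third, the phase explanation is an inference. The section might carry an older visit numbering: its heading of visits 3-6, and the reference in Blood draws to four testing days, fit neither schedule. That is fair. The mismatch is certain; its cause is only very probable. The correction is the same either way.

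Finally, the 150-minute discrepancy can be settled by preferring the more specific text. Agreed; it adds no weight here.

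**Conclusion.** The concern holds. As printed, the rule reaches only the baseline tolerance test in every arm and leaves two of three bariatric tests and one of two non-bariatric tests without the lead-in. The intended plan, very probably a lead-in before every test, is sound.

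The consequence depends on the list being followed literally. In that case the within-group changes in glucose AUC, insulin AUC and insulin sensitivity index are confounded with test preparation, while the contrasts of exercise with standard care and of diet + exercise with diet are largely spared. The protocol gives no basis for estimating how far the AUC or index would shift. The text should be corrected because the rule is operational and governs leading outcomes; it does not call the design into question.

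**What to change.** In Study Testing Visits 3-6, and in any handout to subjects that repeats the rule, replace the visit list with: *each MMTT or OGTT visit (Phases 3, 5 and 7: bariatric visits 3, 4 or 12, and 6 or 14; non-bariatric visits 3, and 6 or 18)*, applied identically in both arms of each pair.

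In the same amendment, reword Blood draws to the grid under Glucose Metabolism tests (fasted, then 30, 60, 90, 120 and 180 minutes), so that one grid is used at every visit.

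The cost is a few words of amendment in two places and a correction to any matching subject instructions. No visits or procedures are added.

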**Urine Collection**:

- Subjects will be provided with a plastic container and asked to collect their first morning urine void. The amount and time urine collection occurs will be recorded and analyzed for nitrogen. In non-bariatric patients, subjects urine collection will be recorded, divided, and analyzed for nitrogen and urine microparticles.

**Fecal Collection:**

- Subjects will be provided with a sterile commode container and asked to collect fecal matter. The amount of fecal matter collected will be recorded and analyzed for gut microbiota.

**Blood draws**:

- In the morning of the 4 study testing days, an IV catheter will be inserted into a vein in either the forearm or the back of the subject’s non-writing hand.
- The IV catheter will be in their arm for the remainder of each visit (about 5 hours), and removed before they leave the CRU.
- During the 4 study visits their blood will be drawn as follows:
  - Fasted
  - Every 30 minutes up to 180 minutes after their drink the beverage
- On each visit, a total of approximately 5-6 tablespoons of blood will be drawn. The blood we take will be tested to measure glucose, insulin, and substances that will help estimate blood glucose control and vessel health.
- A sweet mixed-meal that contains 4 oz of boost meal shake will start the mixed-meal tolerance test (MMTT) for bariatric patients. An oral glucose tolerance test (OGTT) will be given to subjects not undergoing bariatric surgery.
- Non-bariatric patients will have blood drawn (6 ml per draw; 2 draws) to assess blood microparticles, a new biomarker to assess cardiovascular disease risk, at visit 3 and visit 6 (or 18).
- Once the subject drinks the glucose beverage they will return to bed for the remaining blood draws (3-hours)
- When the blood draws are completed they will be fed lunch and discharged to go home.

**Glucose Metabolism tests (i.e. blood sugar):**

*Mixed-Meal Tolerance Test (MMTT) – for subjects undergoing bariatric surgery*

- The MMTT is used to help determine how quickly sugar is removed from the blood and insulin levels rise. After the blood sample is taken for the fasting blood sugar test, the subject will drink a meal shake. Five more blood draws will be taken at 30, 60, 90, 120, and 180 minutes after they receive the drink. The total amount of blood taken is approximately four teaspoons. During this MMTT, the subjects’ metabolic rate, a measure of the amount of energy it takes to burn calories, will be performed at minutes 0, 60, 120 and 180. During this metabolism measure, subjects will wear a canopy that is connected to a special device (metabolic cart) that measures subjects’ exhaled carbon dioxide (CO_2_) and oxygen. These measurements are then used to calculate the amount of calories they burn and will be performed by trained exercise physiologists.

*Oral Glucose Tolerance Test (OGTT) – for subjects not undergoing bariatric surgery*

- The OGTT is used to help determine how quickly sugar is removed from the blood. After the blood sample is taken for the fasting blood sugar test, they will drink a sugary solution.  Five more blood draws will be taken at 30, 60, 90, 120, and 180 minutes after they receive the drink. The total amount of blood taken is approximately 1 1/3 tablespoons. During the OGTT test, the subjects’ metabolic rate, a measure of the amount of energy it takes to burn calories, will be performed at minutes 0, 60, 120 and 180. During this metabolism measure, subjects will wear a canopy that is connected to a special device (metabolic cart) that measures subjects’ exhaled carbon dioxide (CO_2_) and oxygen. These measurements are then used to calculate the amount of calories they burn and will be performed by trained exercise physiologists. The subject’s appetite response to the OGTT will be tested before and after this test.

**Vascular tests:**

*Blood pressure:*

- - The subject’s blood pressure will be taken: before the MMTT and every hour afterwards (at about the same time their blood is being drawn). This test takes about 5 minutes.
- **Augmentation Index (AI)** This measures the pulse wave of the vessel and its characteristics, which is an assessment of the stiffness of the aorta. Researchers will use an aplanation tonometer from SphygmoCor. This is done by placing a blood pressure cuff around the subject’s arm and measuring several waveforms. This will take 2-5 minutes and is comparable to routine blood pressure readings.
- **Pulse Wave Velocity (PWV)** This measures the time difference between the pulse wave at the carotid artery and the pulse wave at the femoral artery. This will allow researchers to assess the “stiffness” of the larger vessels. The shorter the time difference, the stiffer or less elastic the vessels are. Researchers will use the same device as described above. Specifically, a probe that looks like a “fat” pen will be placed over the carotid artery at the neck and a blood pressure cuff will be placed around the upper leg. Researchers measure the time between the heartbeat and when the probe picks up the pulse wave with the tonometer. This will take about 10-15 minutes.
- **Brachial Artery Flow Mediated Dilation (FMD)** Brachial artery diameter is measured using ultrasound at baseline and then after five minutes of forearm ischemia. The subject will supine in bed.  The first measurement is taken (velocity and diameter) and then a blood pressure cuff placed around the forearm is pumped to 200 mm/Hg and held for 5 minutes.  The brachial artery will be observed with ultrasound as the BP cuff is deflated and for 2 minutes post cuff deflation.  This will take approximately 10 minutes. We will perform this procedure just before the beverage, and then again at 1, 2, and 3 hours after the drink.

**Adipose Biopsy***:*

- Adipose biopsy samples will be taken during MMTT/OGTT (Optional). The biopsy involves removal of a very small piece of fat tissue beneath the subject’s skin (referred to as subcutaneous fat) and is about the amount of a pencil eraser. This is performed by way of a needle inserted into your belly area near your navel (belly-button) through a quarter inch skin incision. Local anesthesia will be used to numb the area where the incision will be made. Fat biopsies will be performed on alternate sides of the stomach.
- The abdominal area will be cleansed with an iodine solution. Once thoroughly cleansed and dry, a small amount of numbing (about less than ½ teaspoon of lidocaine), will be injected into the area to be biopsied.
- Once the area is sufficiently numbed, a small incision will be made (approximately 5mm, or less than ¼ of an inch) and a biopsy needle will be inserted in order to obtain approximately 10 grams. Once the biopsy has been completed, slight pressure will be applied to the biopsy area to minimize any bleeding. The area will then be cleansed and a special bandage will be applied to the biopsy site. Subject’s will be asked to keep this bandage on the area for the next 24 hours to reduce risk of bleeding.

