**Collection and/or Storage of Specimens**

**4. How much material (e.g. blood, tissue) will be collected and how will it be collected?**

A total of approximately 600cc of blood will be collected during the entire study (10 weeks) and tested for:

1. Glucose
2. Lipid Profile
3. Blood chemistries
4. C-peptide
5. Free Fatty Acids
6. Insulin
7. Microparticles (for non-bariatric patients only)
8. Biomarkers of inflammatory (e.g. Immune Cells, MCP-1, Hs-CRP, adiponectin, etc.)
9. Adipose tissue fat metabolism markers of inflammation (e.g. MCP-1, UCP-1, etc.)
10. Gut hormones (e.g. GLP-1, Ghrelin)
11. Pregnancy (in females), blood for screening and urine at each admission.

A total of 100cc of urine will be collected during the entire study (10 weeks) and tested for:

1. Microparticles (for non-bariatric patients) will be analyzed using the same exact technique as blood microparticles (ImageStreamX) as routinely done in our UVa Flow Cytometry Core Lab

A total of 8-16 ounces of fecal matter will be collected during the entire study (10 weeks) and tested for gut microbiota (e.g. Bacteroides/Prevotella,Bifidobacterium genus etc.).

A total of 10 grams of adipose tissue will be collected during the pre-intervention testing visit for:

1. PCR analysis of markers of inflammation (e.g. MCP-1, adiponectin, leptin, etc.)

A total of 10 grams of adipose tissue will be collected at the time of surgery (bariatric surgery patients only) for:

1. PCR analysis of markers of inflammation (e.g. MCP-1, adiponectin, leptin, etc.)
2. Isolation of blood vessels to determine insulin-dependent vasodilation of the blood vessels to assess vascular insulin resistance. This will be used to compare in vitro blood vessel response to the intervention when compared to the whole-body in vivo response (Augmentation index).

**5. Could the loss of confidentiality of the subject's health information potentially have a negative impact decisions of health coverage, employment, insurability or any other benefit, or cause social stigmatization*?*** NO

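### The protocol gives two incompatible amounts for the same optional needle fat biopsy, a pencil eraser's worth and about 10 g, and the specimen list and risk table do not cover the procedure fully

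*Protocol*

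**What the plan says.** **Procedure.** In the Protocol, Study Testing Visits 3-6, the Adipose Biopsy bullets (printed under Vascular tests) describe one optional needle procedure done during the meal or glucose test. They begin: "The biopsy involves removal of a very small piece of fat tissue beneath the subject’s skin". The amount "is about the amount of a pencil eraser". The bullets that follow set out the steps: skin cleansing, local anaesthetic and an incision of about 5 mm, after which "a biopsy needle will be inserted in order to obtain approximately 10 grams". They then call for pressure and a bandage kept on for 24 hours to limit bleeding.

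**Specimen list.** Specimen Banking at UVa, item 4, has two adipose entries. The first reads "A total of 10 grams of adipose tissue will be collected during the pre-intervention testing visit", for PCR of inflammation markers. The second reads "A total of 10 grams of adipose tissue will be collected at the time of surgery (bariatric surgery patients only"), for the same PCR and for isolation of blood vessels.

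**Schedule and payment.** The visit overview for non-bariatric subjects marks an adipose biopsy at Visit 3 and again at post-intervention testing. Payment item 2b adds money for the pre-test biopsy and, for completing Phases 4-5, more again ("or $75 if post-test biopsy performed"). The overview for bariatric patients marks a biopsy at Visit 3 and at surgery.

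**Use of the tissue.** Primary Objective 3 relates circulating immune phenotype to the immune composition of fat depots at surgery or at post-intervention testing. Statistical Considerations item 4 places Aim 3 in the primary analysis, while item 2 lists the adipose immune-cell comparisons under secondary objectives.

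**Risks.** The expected-risk table in the Data and Safety Monitoring Plan, item 2.1, covers the IV site, fitness tests, flow-mediated dilation, reproduction, privacy and cardiovascular reactions to exercise. It has no line for the fat biopsy.

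**The concern.** Two descriptions of one invasive step, a few lines apart, differ by more than an order of magnitude on any reasonable reading of the eraser comparison. The larger amount appears again in the specimen section, so it is not a single slip. It cannot be explained as a different procedure either, because the surgical sample has its own entry.

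The amount removed bears on how the procedure is done and on how its risk is described, and the protocol is the reference for both. The risk table cannot settle which amount was weighed, because it does not mention the biopsy at all.

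The specimen list adds a second gap. In non-bariatric subjects, tissue for Objective 3 can come only from the post-intervention needle biopsy. That is the one scheduled fat sample for which item 4 states neither an amount nor an analysis.

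**Working it through.** No sample-size or power figure is involved, and the protocol gives nothing from which the 10 g could be derived. The check is one of consistency.

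**Step 1: turn the eraser comparison into a mass.** The documents give no dimensions, so these are assumptions: a cylinder 5-9 mm in diameter and 5-15 mm long, with fat at 0.90-0.92 g/mL.

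Mass = π × (diameter/2)² × length × density; ratio = 10 g / mass.

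| Assumed eraser (diameter × length) | Volume | Mass | 10 g is larger by |
|---|---|---|---|
| 5 × 5 mm | 0.098 mL | about 0.09 g | 111-113 times |
| 6 × 5 mm | 0.141 mL | 0.13 g | 77-79 times |
| 7 × 10 mm | 0.385 mL | 0.35 g | 28-29 times |
| 8 × 15 mm | 0.754 mL | 0.68-0.69 g | 14-15 times |
| 9 × 15 mm | 0.954 mL | 0.86-0.88 g | 11-12 times |

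For the first row: π × 0.25² × 0.5 = 0.098 mL; × 0.90 = 0.088 g; 10 / 0.088 = 113.

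**Step 2: turn 10 g into a volume.** 10 / 0.92 = 10.9 mL and 10 / 0.90 = 11.1 mL.

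**Step 3: ask how large an eraser would shrink the gap.** For a ratio of exactly ten, the eraser must hold 1 g, that is 1 / 0.90 = 1.11 mL. At 7 mm diameter the length would be 1.11 / (π × 0.35²) = 2.9 cm. To hold the full 10 g it would be ten times as long, about 29 cm. No choice of eraser reconciles the two descriptions.

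**Step 4: set the fat samples side by side.**

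| Sample | Visit schedule | Payment 2b | Specimen Banking item 4 |
|---|---|---|---|
| Bariatric, pre-intervention needle | yes | yes | 10 g |
| Bariatric, surgical | yes | not a separate item | 10 g |
| Non-bariatric, pre-intervention needle | yes | yes | 10 g |
| Non-bariatric, post-intervention needle | yes | yes | not listed |

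The payment totals confirm that two biopsies are intended in non-bariatric subjects: $50 + $50 = $100 without them and $75 + $75 = $150 with both.

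**Step 5: trace the tissue to Objective 3.** The objective uses tissue at surgery or at post-intervention testing. Bariatric patients supply it at surgery. Non-bariatric subjects have no surgery, so their only source is the unlisted sample in the last row.

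**The case against.** The best defence is that the eraser comparison is lay wording. It states no mass or volume, and it sits among phrases addressed to the subject. The only quantities in the protocol, in the procedural steps and in the specimen section, agree on 10 g, so an operator would have to pass over an explicit figure to act on the comparison. The biopsy is also optional, and precautions are given elsewhere: skin cleansing, pressure, a bandage, alternating sides, and exclusion for allergy to the anaesthetic family. This makes an operator error less likely. It does not make the descriptions agree, and precautions do not replace a line in the risk table.

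Several stronger readings are tempting, and the documents do not support them:

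- *That subjects or the IRB were told of a trivial sample.* The consent pages are not available, so what subjects are told cannot be asserted. The protocol itself states 10 g in two places.
- *That the bariatric before/after comparison is biased.* That comparison sets a needle sample against a surgical one, but the protocol states no minimum mass for the assays, and unequal mass does not in itself bias a measure of composition. The surgical entry also has an extra use, vessel isolation, that the needle sample lacks.
- *That Objective 3 is undermined in bariatric patients.* Their tissue for it is taken at surgery, and the objective is not a before/after comparison.
- *That non-bariatric subjects give 20 g against a stated total of 10 g.* The 10 g in item 4 is an amount for one visit. The fault there is an unlisted sample; the figures do not conflict.

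The missing risk entry would be a gap whatever the sample size, so it stands as a separate omission and is not evidence for either amount.

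**Conclusion.** The contradiction stands. One optional needle biopsy is described both as a pencil eraser's worth, about 0.1-0.9 g, and as about 10 g, with the larger figure repeated in the specimen section. The ratio of about 11 to 113 rests wholly on the assumed eraser size and fat density. That the gap exceeds tenfold holds across the whole range tried and fails only for an eraser of about 1.1 mL or more.

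Two omissions also stand and need no assumption: the non-bariatric post-intervention sample is missing from the specimen list, and the biopsy is missing from the expected-risk table.

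The link to a primary objective is narrow. It runs through the non-bariatric post-intervention biopsy alone, in those subjects who agree to it. This should be corrected because it concerns an invasive procedure and costs almost nothing to put right. It does not show that any planned analysis is invalid.

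**What to change.** 1. Reconcile the two Adipose Biopsy descriptions and Specimen Banking item 4 to one stated amount for the needle biopsy. Which amount is right is for the investigator and the IRB to decide.
2. Add the non-bariatric post-intervention biopsy to item 4, with its amount and planned analyses, so that the list matches the visit schedule and Payment item 2b.
3. Add the fat biopsy to the expected-risk table in item 2.1 of the Data and Safety Monitoring Plan, described for the amount settled in step 1.
4. Check that the consent form, not available here, uses the same amount.

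The cost is a wording amendment, with no new procedure, visit or sample. Recording the mass of each sample would be useful, but it is a preference and the correction does not depend on it.
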